**Fig. 2 Fig2:**
[figure not shown]
Schedule of enrolment, interventions, and assessments. 1) Shoulder pain and disability index; 2) Numeric pain rating scale; 3) Active range of motion; 4) Pain pressure threshold

### Sample size

In order to calculate the number of subjects to be included in this study an alpha value of 0.05 and power of 80% was chosen together with a minimal clinically important difference of 10 points on the SPADI scale with standard deviation of 13.5 points [26]. An initial number of 28 participants in each group was required based on this calculation. With an estimated 20% loss to follow-up, we planned to recruit a total of 70 subjects (35 in each group).

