### Statistical analysis

Data will be analysed using the Statistical Package for Social Science software (SPSS v.20, Inc., Chicago, USA). The analyses will be conducted considering a statistically significant *p*-value ≤0.05. Data normality of the study will be assessed with the Kolmogorov-Smirnov test and homogeneity with the Levene’s test. The results will be reported as the mean with corresponding 95% confidence interval. Intention-to-treat analysis will be conducted so that all patients are analysed within their group allocation. Drop-outs and their reasons will be informed. All data input will be kept in two different files (double data entry) that will be updated every week by a research assistant.

A two-way analysis of variance will be conducted to assess between and within groups differences. For the primary outcome measures (SPADI and NPRS) a 2 × 3 ANOVA with treatment group (EG versus CG) and time (baseline, end of the treatment and follow-up) factors will be performed. Separate 2 × 2 ANOVA will be used for ROM (baseline and end of the treatment period), and a 2 × 3 ANOVA will be conducted for self-efficacy (baseline, end of the treatment period and follow-up). Additionally, appropriate post-hoc tests (Bonferroni) will be used if prior analysis indicates significant differences. GROC analysis will be conducted using descriptive statistics and participants will be classified according to treatment success. Those reporting + 5 or more will be classified as successful. Within groups differences will be calculated at the end of the treatment period and follow-up, and effect sizes will be calculated using Cohen effect size (0.2–0.5: small effect, 0.5–0.8: moderate effect, 0.8 or more: large effect size).

A second study will explore changes in expectation throughout treatment descriptively and whether those differences are associated with SPADI, NPRS and group allocated. Therefore, an ANCOVA will be conducted to analyze the influences of covariates (expectation and self-efficacy) on SPADI and NPRS. A separate 2 × 3 ANOVA will be used to examine PPT measurements in the three different body areas. Post-hoc tests (Bonferroni) will be used if prior analysis indicates significant differences.

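### The stated 80% power belongs to a single unadjusted two-group SPADI comparison that the analysis section does not plan; the planned ANOVA with conditional Bonferroni tests has no stated power

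*Protocol article*

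**What the plan says.** The Sample size section of the protocol article states that "an alpha value of 0.05 and power of 80% was chosen", together with a "minimal clinically important difference of 10 points on the SPADI scale" and a spread given "with standard deviation of 13.5 points". It concludes: "An initial number of 28 participants in each group was required based on this calculation". A 20% allowance for loss takes this to 35 per group, 70 in total. It mentions no repeated measures, no correlation between visits and no multiplicity adjustment.

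The Statistical analysis section sets significance at p ≤0.05. It assigns the assessment of between-group and within-group differences to a two-way analysis of variance. For SPADI and NPRS, both primary, "a 2 × 3 ANOVA with treatment group (EG versus CG) and time (baseline, end of the treatment and follow-up) factors will be performed". It then adds that "appropriate post-hoc tests (Bonferroni) will be used if prior analysis indicates significant differences". It does not say which ANOVA term decides, which post-baseline visit is primary, or how many comparisons the Bonferroni correction covers.

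**The concern.** The only power figure in the protocol should describe the test on which the trial will be judged. A 10-point difference between two groups is a contrast at one visit. The ANOVA terms are different quantities. The group-by-time interaction, on 2 degrees of freedom, says that the two profiles differ but not where or by how much. The group main effect averages in baseline, where randomised groups should not differ. The only written route from the ANOVA to a difference at a given visit is the post-hoc step, which depends on a prior significant result and carries a Bonferroni correction. The sizing allows for neither.

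SPADI is the only outcome that was sized. A null result could be read as evidence against MWM on the strength of an 80% power that the planned procedure may not have.

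**Working it through.** **Inputs from the Sample size section:** alpha 0.05, power 80%, difference 10, SD 13.5, 28 evaluable per group. **Assumed, because the article does not give them:** two-sided testing (one-sided would give 23 per group, which does not match 28); 13.5 as the SD of the SPADI score at each visit; equal correlation ρ between visits, taken as 0.3, 0.5 or 0.7; the size m of the Bonferroni family.

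**1. The plan's own figure.** n = 2 × [13.5 × (1.960 + 0.842)/10]² = 28.6 per group, against 28 stated. At n = 28 the standardised difference is 10/(13.5 × √(2/28)) = 2.77. Power is Φ(2.77 − 1.96) = 79% by the normal formula and 77.7% by the noncentral t. Allowance for loss: 28/0.80 = 35. The figure is therefore that of one unadjusted two-group comparison.

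**2. Bonferroni alone (t-test at 0.05/m).**

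| m | alpha | 28 per group | 35 per group |
|---|---|---|---|
| 1 | 0.05 | 78% | 86% |
| 2 | 0.025 | 68% | 79% |
| 3 | 0.0167 | 62% | 74% |

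**3. The ANOVA terms alone, 28 per group.** With Dⱼ the group difference at visit j and D̄ its mean over the three visits, the interaction has noncentrality λ = (n/2) Σ(Dⱼ − D̄)² / [σ²(1 − ρ)] on 2 and 108 degrees of freedom. For differences 0/10/10 at baseline, end of treatment and follow-up, D̄ = 6.67 and Σ(Dⱼ − D̄)² = 66.7. At ρ = 0.5, λ = 14 × 66.7/(182.25 × 0.5) = 10.2.

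| Term | Effect | ρ = 0.3 | ρ = 0.5 | ρ = 0.7 |
|---|---|---|---|---|
| Interaction | 0/10/10 | 66% | 81% | 96% |
| Interaction | 0/10/5 | 53% | 69% | 90% |
| Group main effect | 0/10/10 | 70% | 60% | 53% |

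The main effect is weak because including baseline dilutes the contrast from 10 to 6.67 points.

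**4. Interaction significant at 0.05, then the end-of-treatment t-test at 0.05/m.** Simulated with 28 per group and 20,000 trials per cell. Repeat runs agree to about one point.

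| Effect | m | ρ = 0.3 | ρ = 0.5 | ρ = 0.7 |
|---|---|---|---|---|
| 0/10/10 | 1 | 55% | 65% | 76% |
| 0/10/5 | 1 | 48% | 59% | 72% |
| 0/10/0 | 1 | 59% | 68% | 76% |
| 0/10/10 | 2 | 49% | 58% | 66% |
| 0/10/5 | 2 | 44% | 53% | 63% |
| 0/10/0 | 2 | 54% | 61% | 67% |

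Every cell is below 80%, including those with no Bonferroni correction (m = 1).

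**5. A lenient reading.** Suppose that any significant group or interaction term permits the post-hoc tests and that a difference at either post-baseline visit counts, with m = 2. Power at ρ = 0.3, 0.5 and 0.7 is then 84%, 81% and 79% if the effect is maintained, 65%, 66% and 67% if it halves, and 62%, 66% and 69% if it vanishes.

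**The case against.** A reader might infer that the protocol declares a between-group difference only through Bonferroni-corrected tests, so that its power is 55–70% and a true 10-point effect is missed about 40% of the time. The text does not support that. The Statistical analysis section gives the between-group assessment to the ANOVA itself and introduces the post-hoc tests as an addition. It states no family size. With two groups there is one between-group contrast per visit, so a correction applied within visit would leave alpha at 0.05. If the interaction test decides, power for a maintained effect is 81% at ρ = 0.5 and 96% at ρ = 0.7. The lenient reading in step 5 also gives about 80% when the effect is maintained. If nobody is lost, 35 per group give 79% at alpha 0.025.

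It can also be said that sizing on a simpler test than the final model is common, that nothing in the arithmetic of the Sample size section is at fault here, and that a condensed article may leave the deciding term and the family to a fuller document.

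These points stand against any single figure for the loss. They do not remove the mismatch, which lies between two statements in the article: the sizing describes an unconditional, unadjusted comparison, and the analysis section describes a different procedure. Nor does a family of one rescue a visit-specific claim made through the interaction, since power there is still 48–76%. The no-loss case sets aside the plan's own 20% allowance.

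**Conclusion.** The point holds as a mismatch between the power statement and the planned analysis. It does not establish one corrected power. The stated 80% is the power of a two-group SPADI comparison that is not planned. For a 10-point end-of-treatment difference declared through a significant interaction and then a post-hoc test, power at 28 per group is below 80% in every scenario examined: about 48–76% with no correction and about 44–67% with a family of two. Bonferroni alone, without the prior ANOVA condition, gives 68% for two comparisons and 62% for three. These figures rest on assumed correlations of 0.3–0.7, equal SDs of 13.5 at each visit, and an effect that persists, halves or vanishes at follow-up. Other defensible readings reach 80% or more. It should be put right before analysis, because otherwise the reading of a null result would depend on a rule that has not been settled.

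**What to change.** In the Statistical analysis section, name one EG–CG contrast in SPADI at one post-baseline visit (for example the end of treatment; the choice is the sponsor's). Test it at two-sided 0.05, not conditional on the ANOVA and outside the Bonferroni family. Describe the other visit and the ANOVA terms as supportive. State how NPRS, also listed as primary, is handled, so that it is clear whether the SPADI contrast keeps the full 0.05. The existing sizing then describes the test that is used, with 78–79% power at 28 evaluable per group.

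Alternatively, keep the ANOVA followed by Bonferroni tests. In that case specify the deciding term, the visit and the family, and restate the power in the Sample size section for that rule with its assumed correlation. For the interaction followed by an end-of-treatment test in a family of two, at correlation 0.5, that is about 53–61% depending on the course of the effect.

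Either change is a matter of wording and needs no extra participants. The cost is that one visit becomes supportive, or that the stated power becomes less favourable.

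### The SPADI sample size is rounded down by one or two participants per group, and its inputs do not define the power of the planned 2 × 3 ANOVA

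*Protocol article*

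**What the plan says.** The Sample size section of the protocol article sets out its main inputs in these words: "alpha value of 0.05 and power of 80% was chosen together with a minimal clinically important difference of 10 points on the SPADI scale". The SD it uses is 13.5. From these it concludes: "An initial number of 28 participants in each group was required based on this calculation". It allows for an estimated 20% loss to follow-up and reports that "we planned to recruit a total of 70 subjects (35 in each group"). It gives no sidedness, formula or software, and does not say whether the SD is that of scores at one visit or of change from baseline.

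The Statistical analysis section sets the significance rule: "The analyses will be conducted considering a statistically significant *p*-value ≤0.05". For SPADI and the pain scale it plans a 2 × 3 analysis: "ANOVA with treatment group (EG versus CG) and time (baseline, end of the treatment and follow-up) factors will be performed".

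**The concern.** There are two separate questions.

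- **Arithmetic.** A required sample size is rounded up. If the stated inputs give more than 28, then 28 per group does not reach the stated 80%. Because 28 is carried straight into the dropout allowance, the recruited number inherits the gap.
- **Match between sizing and analysis.** One difference and one SD define the power of a single comparison of two means. The group-by-time test in a 2 × 3 ANOVA also depends on how strongly a patient's SPADI scores correlate across visits, and on which SD was used. The 80% is therefore not, as it stands, the power of the test that will be run.

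The stake is modest. If the result is null, readers will judge it against the stated power, so that figure should be reproducible and should belong to the analysis reported.

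**Working it through.** **Inputs from the protocol article.** Difference 10, SD 13.5, alpha 0.05, power 80%, 1:1 allocation, 20% loss (all from Sample size). Two-sided testing is an assumption; it fits an ANOVA F-test at the 0.05 level.

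**1. The plan's own figure.** Normal formula:

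n = 2 × (1.960 + 0.8416)² × (13.5/10)² = 28.61 per group, which rounds up to 29.

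The noncentral-t solution is 29.60, which rounds up to 30. One-sided alpha gives 23 (normal) or 24 (t-test), so it does not explain 28. The most likely source of 28 is 28.61 rounded down.

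**2. Dropout.** 28/0.8 = 35.0, which reproduces 35 per group and 70 in total. Starting from 29 or 30 gives 29/0.8 = 36.25 (37) or 30/0.8 = 37.5 (38) per group, that is 74 or 76 in total.

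**3. Power by evaluable number per group (two-sided).**

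| Evaluable per group | Normal formula | t-test |
|---|---|---|
| 28 | 79.1% | 77.7% |
| 29 | 80.5% | 79.2% |
| 30 | 81.8% | 80.5% |
| 35 | 87.3% | 86.3% |

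With 28 per group the t-test has 80% power for a difference of 10.3 points rather than 10.

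**4. The group-by-time test in the 2 × 3 ANOVA, 28 per group.** Assumptions, since the article gives none: a between-group difference of 0 at baseline and 10 at both later visits, equal variances, and the same correlation r between any two visits. The test is F on 2 and 108 degrees of freedom, with noncentrality

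λ = (n/2) × Σ(d − mean d)² / [σ²(1 − r)], where σ is the SD at each visit.

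Here Σ(d − mean d)² = 66.67 and n/2 = 14, so the numerator is 933.3.

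- *If 13.5 is the SD at each visit*, σ² = 182.25. At r = 0.3, λ = 933.3/(182.25 × 0.7) = 7.32 and power is 66%.
- *If 13.5 is the SD of change*, 2σ²(1 − r) = 182.25, so σ²(1 − r) = 91.125 and λ = 933.3/91.125 = 10.24 whatever r is. Power is 81%.

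**5. Baseline-adjusted ANCOVA of SPADI at end of treatment, 28 per group, 53 df.** The residual SD is 13.5 × √(1 − r²) if 13.5 is the SD at each visit, and 13.5 × √((1 + r)/2) if it is the SD of change. For example, at r = 0.3 these are 12.88 and 10.88.

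| r | ANOVA, per-visit SD | ANOVA, change SD | ANCOVA, per-visit SD | ANCOVA, change SD |
|---|---|---|---|---|
| 0.3 | 66% | 81% | 81% | 92% |
| 0.4 | 73% | 81% | 84% | 90% |
| 0.5 | 81% | 81% | 88% | 88% |
| 0.6 | 90% | 81% | 93% | 86% |
| 0.7 | 96% | 81% | 97% | 84% |

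**The case against.** The strongest reply is that this is a rounding remark. The gap is one or two participants per group, and by the formula that comes closest to 28 the power is 79.1%. The 20% loss is itself only an estimate: by the t-test, 30 evaluable per group instead of 28 is enough for 80%, and with no loss power is 86%. Sizing a repeated-measures trial by a two-group comparison is also a common simplification, and a journal article need not print a correlation. All of this stands, and it sets the size of the point: no recruitment decision turns on it. It does not make 28 the number that the stated inputs require.

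A reader might go further and infer that the planned ANOVA has only 66–73% power. The documents do not support that. Those values need 13.5 to be the SD at each visit and the correlation to be 0.3–0.4, and the article states neither. Under the same model power is 90–96% at correlations of 0.6–0.7, and about 81% at every correlation if 13.5 is the SD of change.

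**Conclusion.** The point holds as a small discrepancy plus an unspecified link between sizing and analysis. Assuming two-sided testing, the stated inputs need 29 or 30 evaluable per group. The planned 28 gives about 78% power (t-test) to 79% (normal formula), a shortfall of roughly 1–2 percentage points. The dropout inflation is correct.

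The power of the 2 × 3 ANOVA cannot be read from the sample size statement. Over the range examined it lies between 66% and 96% on one reading of the SD and at about 81% on the other, for a 10-point effect at both later visits and equal correlations. The planned test is not shown to be underpowered, and the trial is not shown to be too small.

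**What to change.** Leave recruitment at 70 and make three changes of wording, before outcome data are seen:

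1. Restate the power: 35 per group, with 28 evaluable after 20% loss, gives about 78% power for a 10-point SPADI difference (SD 13.5, two-sided alpha 0.05, t-test).
2. Say whether 13.5 is the SD of SPADI at a visit or of change from baseline.
3. Name baseline-adjusted ANCOVA of SPADI at end of treatment as the powered analysis, and give its power under the SD that is meant. For correlations of 0.3 to 0.7 this is 81% to 97% with a per-visit SD, or 92% down to 84% with a change-score SD, so at least 81% either way.

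The cost is a few sentences. The baseline SPADI score is already collected, so no patients or visits are added. The unadjusted power statement becomes slightly less favourable, and the ANCOVA recovers the shortfall.

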### Recruitment

Subjects will be recruited through a range of strategies. Initially, consecutive patients with shoulder pain seeking treatment at a private physiotherapy practice that agree to participate and fit the inclusion criteria, will be invited to enrol. Second, a research assistant will contact local orthopaedic specialists and inform about the study with an aim to request referrals. Third, study advertisements will be released on social media and a local printed newspaper. Lastly, a partnership established with the health secretary of *São Leopoldo* city will enable subject referral. Therefore, patients fitting the study criteria, referred to the local public physiotherapy service, will be invited to participate.

### Allocation

Participants will be stratified by pain followed by sequence generation, using a computer generated random numbers. In order to reduce predictability of random sequence, blocks of 4 and 6 random numbers will be used. Allocation sequence will be placed in sequentially numbered opaque, sealed envelopes. All allocation procedures will be conducted by a research assistant not involved in any other aspect of the study.

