### Study settings

The study will occur in two different locations, at the physiotherapy laboratory 1 at *Faculdades Integradas de Taquara* and a private practice (*Clínica Albrecht*). The Recruiment process and flow through study is depicted in Fig. 1.

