### Participant timeline

The enrollment process will begin from the end of February 2020. After entering the study, participants will have the following outcomes assessed at baseline: SPADI, NPRS, AROM, PPT, expectations and SE; at the end of the treatment period: SPADI, NPRS, AROM, PPT and GROC; and at one month follow-up: SPADI, NPRS, and GROC. Expectation is the only outcome measure to be collected during the third week of treatment. Figure 2 depicts enrolment, interventions and assesssments timeframes throughout the study. Participants will attend ten individual sessions, twice a week (approximately 40 min each), in either of the available treatment sites, according to their geographic locations (see study settings). For the follow-up, participants will be contacted by a research member via email or mail to fill out the respective outcome measures. A telephone call will be made for participants that miss one treatment session without providing explanations.

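### Randomisation is stratified by pain but not by site, and the stated primary ANOVA has no site term, so a chance site imbalance between arms is neither prevented nor adjusted for (minor).

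*Protocol article*

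**What the plan says.** The Allocation section of the protocol article gives the scheme: "Participants will be stratified by pain followed by sequence generation, using a computer generated random numbers". Blocks are of 4 and 6, in sealed, numbered envelopes. Site is not mentioned there.

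Study settings says "The study will occur in two different locations" and names a faculty physiotherapy laboratory and a private practice. Participant timeline says that the ten sessions are attended "in either of the available treatment sites, according to their geographic locations".

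Statistical analysis specifies a 2 × 3 ANOVA for SPADI and NPRS, with treatment group and time as its factors. No section of the article stratifies by site, gives a site its own sequence, or adjusts for site.

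**The concern.** A participant's site follows from where they live, not from randomisation. Blocking within pain strata keeps the arms close in size within each pain stratum, but does nothing to keep them close in size within each site. By chance, more of one arm could be treated at the laboratory and more of the other at the private practice.

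Site could plausibly be related to outcome. The settings differ in type, the mobilisation and the exercise load are individualised, and both primary outcomes are self-reported. If it is related, two things are at stake. Variation between sites stays in the error term, so the comparison is less precise than it could be. And if a visible imbalance did arise, a reader would ask how much of the result it explains, and the stated model could not answer.

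**Working it through.** **Inputs.** From Sample size: "an alpha value of 0.05 and power of 80% was chosen", a "minimal clinically important difference of 10 points on the SPADI scale" "with standard deviation of 13.5 points", and "An initial number of 28 participants in each group was required based on this calculation"; then 20% loss, giving 35 per arm and 70 in total. From Allocation: pain strata, blocks of 4 and 6. Not given, so assumed: the site split (50/50 to 80/20), two equal pain strata, and a between-site difference in mean SPADI change of 5 to 10 points.

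**1. The plan's own figure.** n per arm = 2 × (13.5 × (1.960 + 0.842) / 10)² = 28.6, which rounds up to 29; the plan states 28. With 28 per arm, power is 79.1% by the normal approximation. Then 28 / 0.8 = 35 per arm and 70 in total, as stated. The sample size reproduces to within one participant per arm, and the site question does not change it.

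**2. Spread of the site imbalance.** Suppose K of the 70 participants are treated at site A and allocation ignores site. The number X of these in one arm of 35 is hypergeometric, with variance 35 × (K/70) × (1 − K/70) × 35/69. The between-arm difference in site share is (2X − K)/35, so its SD is 2 × SD(X)/35.

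- K = 35 (50/50): Var(X) = 4.44, SD(X) = 2.11, SD of the difference = 12.0 percentage points.
- K = 14 (80/20): Var(X) = 2.84, SD(X) = 1.69, SD of the difference = 9.6 percentage points.

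**3. Chance of a difference of 20 points or more.**

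| Site split | P(20 points or more) | P(strictly more than 20 points) |
|---|---|---|
| 35/35 | 15.1% | 5.5% |
| 30/40 | 9.0% | 9.0% |
| 25/45 | 13.4% | 4.5% |
| 14/56 | 3.4% | 3.4% |

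The figures jump because only certain differences are possible. At 35/35 and 25/45, an exact 20-point difference can occur and carries much of the probability. A simulation with blocks of 4 and 6 within two pain strata, and the site total left random, gives 11% (50/50) falling to 4% (80/20). A fair range is 3 to 15%.

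**4. Effect on the SPADI comparison.** Shift = imbalance × site difference.

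- 0.20 × 5 = 1 point; 0.20 × 10 = 2 points.
- A typical (1 SD) imbalance at 50/50: 0.12 × 10 = 1.2 points.
- Standard error of the group difference: 13.5 × √(2/35) = 3.2 with 35 per arm; 13.5 × √(2/28) = 3.6 with 28.

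**5. Precision recoverable.** With a 50/50 split, the between-site variance is 0.25 × D², where D is the site difference.

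- D = 10: residual SD = √(182.25 − 25) = 12.54; standard error with 35 per arm falls from 3.23 to 3.00, about 7%.
- D = 5: residual SD = √(182.25 − 6.25) = 13.27; standard error falls from 3.23 to 3.17, about 2%.

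With a less even split the gain is smaller: at 80/20 and D = 10, the residual SD is √(182.25 − 16) = 12.89, a gain of about 4%.

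**6. What site-by-pain stratification does.** Simulated with the same blocks, the SD of the site imbalance drops to about 3 percentage points, a difference of 10 points or more occurs in about 0.1% of trials, and none of 20 points or more occurred in 5,000 runs.

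**The case against.** The strongest reply is that nothing here is invalid. Pain is a sensible stratifier, being the baseline of a primary outcome, and the sequence is random, blocked and concealed. The expected site imbalance is zero, and chance imbalance in any prognostic factor is part of the sampling error that the test and confidence interval already carry. A reader might infer that a site imbalance would pass for a treatment effect. The documents do not support that in the sense of bias: the type I error is not inflated. This part of the objection stands, and it limits the point to precision and credibility.

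The size is also conditional. The article gives neither the site split nor any evidence that outcomes differ by site, and the upper assumption of 10 points equals the trial's whole target effect. That stands too, which is why ranges are shown.

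Three further inferences are tempting but not established:

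- That site tracks patient source. Recruitment lists several sources, beginning with "consecutive patients with shoulder pain seeking treatment at a private physiotherapy practice", but site follows geography and no source is tied to a site.
- That therapists differ by site. The Blinding section speaks of one treating research assistant in the singular, so this is open.
- That one envelope series shared by two sites would be used out of order. Allocation and Blinding give all allocation to one independent assistant, who can keep a series in order; nothing says that envelopes are held or opened separately at each site.

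Finally, the article is condensed, and an analysis plan not shown might add a site term. If so, the analysis half of the fix is already met. The article itself, however, fixes both the stratification factor and the factors of the ANOVA, and site is in neither.

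**Conclusion.** The point holds as a minor, cheap improvement. As written, the plan neither prevents a chance site imbalance nor adjusts for one. An imbalance large enough to be noticed is not rare, but its likely effect on the result is small: under the assumed site differences, a 20-point imbalance moves the SPADI difference by well under one standard error, and the precision to be gained is a few per cent at most.

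The size rests on the assumed site split and site difference, and on taking the sample-size SD of 13.5 as the total SD of the compared score. If outcomes do not differ between sites, the imbalance has no effect on the expected comparison. The finding does not show that the randomisation is faulty, that the comparison is biased, or that the sample size is inadequate.

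**What to change.** For participants not yet randomised, have the independent assistant generate a separate sequence for each combination of site and pain stratum, keeping blocks of 4 and 6. With two pain levels that makes four lists, about 17 participants each if evenly filled (70 / 4 = 17.5). Keep all allocations already made; the registration table lists the trial as recruiting, so there may be some. In either case, state that site enters as a factor in the between-arm comparisons of SPADI and NPRS.

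The cost is new lists and envelopes and a sentence each in Allocation and Statistical analysis. The total stays at 70. The downsides are more part-filled final blocks, so arm sizes may differ by a few participants, and one degree of freedom spent in the model.
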